#### 2.5.4 Secondary endpoints of the main trial.

Excretion of calcium in 24h urine at seven-time points before and after SGLT-2 inhibitor therapyExcretion of magnesium in 24h urine at seven-time points before and after SGLT-2 inhibitor therapyExcretion of citrate in 24h urine at seven-time points before and after SGLT-2 inhibitor therapyExcretion of uric acid in 24h urine at seven-time points before and after SGLT-2 inhibitor therapyeGFR (CKD-EPI) before and after therapyTolerance to treatmentQuality of Life Assessment*Metabolomics* analysis out of blood and urine samples at four time points before and two-time points after dapagliflozin therapy.

#### 2.5.5 Further Study Procedures.

Prospective collection of baseline variables

AgeNumber and compositions of previous stone formationsComposition of last stoneDiabetes disease type I and IITherapy tolerabilityQuality of life assessment using the SF36 questionnaire

#### 2.5.6 Metabolomics analysis.

The metabolomics analysis in this study focuses on specific metabolites and metabolic pathways derived from blood and urine samples. From blood samples, the analysed pathways include glyoxylate and dicarboxylate metabolism, glycine, serine and threonine metabolism, glutathione metabolism, phenylalanine metabolism, beta-alanine metabolism, the citrate cycle (TCA cycle), and several others (full list provided in the supplemental materials). From urine samples, the analysis includes amino acids (e.g., α-aminobutyric acid, isoleucine, methionine, phenylalanine, valine), creatinine, citrate, glycine, hippurate, and additional metabolites. The complete list of planned analyses has been provided in S2. Appendix.

### 2.6 Study schedule

We plan to do blood- and 24-hour-urine screenings including oxalate and citrate as well as metabolomics tests out of blood and urine samples at crucial points of time of the study to get baseline and therapeutic data of the participants. The primary endpoint is confirmatory and is the reduction of oxalate in the *Verum* vs. Placebophase, i.e., Dapaglifozine vs. placebo which will be compared with a two sided-t-test.

#### 2.6.1 Exploratory phase.

Before the main trial is about to begin there will be an exploratory part of the study. 22 participants with a diagnosis of cardiomyopathy, a given indication for dapagliflozin, and that as well might benefit from the therapy, will be included in one group. For 6 weeks all patients will get an oral therapy of 10mg dapagliflozin daily. To get baseline data of all participants blood and urine samples will be collected before the beginning of the exploratory phase; the treatment response will be evaluated by blood- and urine tests after 4 and 6 weeks of therapy. With the collected data an interim analysis targeting the pathophysiology of urolithiasis as well as the effect mechanism of dapagliflozin will be calculated. Only if the data of the exploratory phase shows a positive effect of dapagliflozin on the excretion rate of oxalate, calcium, phosphate, and uric acid the next part of the main trial will begin.

Patients who already participated in the exploratory phase won’t be treated differently and will have to run through all the following phases whether they already received the trial treatment or not—that way the blinding is still given and whether participants nor investigators can extrapolate their status.

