#### 2.6.2 Main trial phase.

The main trial will start with wash-out phase I. All patients will receive blood- and 24-hour-urine screenings in week 6 (respectively week 12 overall) to get baseline data. In preparation for the treatment phase I all participants will receive a daily oral placebo administration over the whole period and will be randomized in two groups.

In week 13 the treatment phase I will start and group 1 will receive oral therapy with 10mg of dapagliflozin while group 2 will get an oral placebo administration daily; the treatment response will be evaluated by blood- and urine test after 4 weeks of therapy (respectively week 16 overall) and in the beginning of in washout phase II (respectively week 21 overall). The same test as before will be performed after 6 weeks (respectively week 26 overall) to gain baseline data for treatment phase II. In preparation for the treatment phase II, all participants will receive a daily oral placebo administration. will receive a daily oral placebo administration.

In the end, we will perform treatment phase II with an oral administration of 10mg of dapagliflozin for group 2 and daily placebos for group 1. The treatment response will be evaluated by blood- and urine tests after 4 weeks of therapy (respectively week 30 overall). Finally, the same tests as before will be performed in wash-out phase III in weeks 1 and 6 (respectively weeks 35 and 40 overall). This way we will get data of the non-therapy periods and of the outcome that will be caused by the dapagliflozin therapy. For each patient, a comparison will be made between the excretion of the electrolytes and molecules of the primary and secondary endpoints under dapagliflozin therapy vs. oral placebo administration.

Throughout the whole study procedure, all participants will be advised to follow dietary instructions as recommended in the urolithiasis guidelines of 2023 [62]. The requested measures will include a balanced diet including a high ratio of vegetables and fibers, a low-fat diet, a calcium intake of about 1.0 to 1.2g per day, a reduced intake of salt up to a maximum of 4.0 to 5.0g per day and an intake of animal proteins of 0.8 to 1.0g per kg per day may reduce stone development risk. Furthermore, patients are strongly advised to not lose or gain weight tremendously throughout the trial process so that the date will be comparable over the whole trial period.

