#### 2.7.4. Dietary compliance monitoring.

All participants will receive clear, written dietary instructions and regular reminders during study visits to promote adherence. Compliance will be monitored through dietary adherence questionnaires completed at each study visit throughout the study. Although perfect adherence cannot be guaranteed, any non-compliance will be documented and addressed with participants as needed. Significant deviations from the dietary instructions will be considered during the analysis phase as potential confounding factors to ensure a robust interpretation of the results.

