#### WP1. Screening (Pre-study phase, 4 Months).

**Objective:** WP1 includes a prospective analysis of all patients of the Division of Cardiology of the General Hospital of Vienna with a diagnosed cardiomyopathy, diabetes mellitus II and no established SGLT-2 inhibitor therapy. Furthermore, also patients of the Department of Urology of the General Hospital of Vienna with at least one event of urolithiasis and a high risk of reoccurrence will be screened in preparation for the main trial. Baseline data as mentioned earlier of all study participants of the exploratory phase are collected **Methods:** 22 potential study participants fulfilling defined exclusion and inclusion criteria and willing to participate in the exploratory phase will be recruited. Pre-screening of potential participants of the main trial.

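### The exploratory phase provides no on-diet period before its baseline urine, so its single-group change cannot separate dapagliflozin from the dietary instructions

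*Protocol article*

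**What the plan says.** Protocol article, section 2.6.1: the exploratory participants "will be included in one group", and "For 6 weeks all patients will get an oral therapy of 10mg dapagliflozin daily". On the baseline it says: "To get baseline data of all participants blood and urine samples will be collected before the beginning of the exploratory phase". Response is measured after 4 and 6 weeks on the drug. WP1, headed as a four-month pre-study screening phase, confirms the placement: "Baseline data as mentioned earlier of all study participants of the exploratory phase are collected".

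Diet, section 2.6.2: "Throughout the whole study procedure, all participants will be advised to follow dietary instructions as recommended in the urolithiasis guidelines of 2023". The measures listed there cover vegetables and fibre, fat, calcium, salt and animal protein. Section 2.7.4 adds: "All participants will receive clear, written dietary instructions and regular reminders during study visits to promote adherence".

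The only preparation described before the exploratory phase is in section 2.4.1, where potentially interfering drugs are paused for four weeks. Diet is not mentioned there. In the main trial the baseline is taken in week 6 of wash-out I, on placebo (section 2.6.2, WP4).

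The exploratory result is used twice. Section 2.6.1 makes the main trial conditional on a positive effect on oxalate, calcium, phosphate and uric acid excretion. Section 2.3.2 and WP3 recalculate the main-trial sample size from the observed effect, although section 2.3.2 also lists a fixed expected effect of 25%.

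**The concern.** A before/after change in one group credits the drug with everything else that changes between the two measurements. If the baseline urine is taken before the study begins and the dietary advice runs with the study, diet and dapagliflozin both change between baseline and week 4. There is no control group from which the diet part could be estimated and removed.

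The article itself treats diet as relevant to the measurement. Section 1.2.2 offers binding of oxalate in the gut by dietary calcium as an explanation for lower stone risk. Section 2.6.2 gives within-participant comparability over the whole trial as a purpose of the diet, and a baseline taken off the diet defeats that purpose.

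At stake are two planning decisions: whether the main trial opens, and how large it is. The estimate of the treatment effect in the main trial is not at stake. There both periods are on the diet, the baseline follows a six-week lead-in, and placebo is the comparator.

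**Working it through.** **Sequence on the natural reading**

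| Time | Diet instructions | Dapagliflozin |
|---|---|---|
| Exploratory baseline (WP1, pre-study) | no prior on-diet period described | no |
| Exploratory weeks 4 and 6 | yes | yes |
| Main-trial baseline (week 6 of wash-out I) | yes | no |
| Main-trial treatment periods | yes | drug or placebo |

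In the first pair of rows, diet and drug change together. In the second pair only the drug differs between the arms.

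**Reproducing the plan's own figures.** Inputs from section 2.3.1 and Table 1: SD 0.20 in one condition and 0.20 × (1 + d) in the other, correlation 0.1, power 90%, paired t-test.

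SD of the difference = √[0.20² + (0.20(1 + d))² − 2 × 0.1 × 0.20 × 0.20(1 + d)].

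For d = 0.25 this is √(0.0400 + 0.0625 − 0.0100) = √0.0925 = 0.3041, so the standardised effect is 0.25/0.3041 = 0.822. The noncentral t distribution at two-sided 0.05 gives n = 18. The five rows of Table 1 come out as 86, 42, 26, 18 and 14, all as printed. The stated two-sided 0.025 gives 102, 49, 30, 21 and 17 instead, so 0.05 is used below.

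**Adding a diet effect.** The documents give no size for it, so the diet values are assumptions. Apparent reduction = 1 − (1 − drug) × (1 − diet). The main trial is sized on the apparent reduction for 90% power. Real power is then computed at the true drug effect. N is evaluable participants, before the 20% dropout addition.

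True drug effect 15%; correct N = 42:

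- Diet lowers oxalate by 5%: 1 − 0.85 × 0.95 = 0.1925. SD of difference 0.2955; N = 27; real power 74%.
- Diet lowers oxalate by 10%: 1 − 0.85 × 0.90 = 0.235. SD of difference 0.3019; N = 20; real power 60%.
- Diet raises oxalate by 5%: 1 − 0.85 × 1.05 = 0.1075. SD of difference 0.2832; N = 75, so the trial would be larger than needed.

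True drug effect 10%; correct N = 86:

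- Diet lowers oxalate by 5%: 1 − 0.90 × 0.95 = 0.145; N = 44; real power 63%.
- Diet lowers oxalate by 10%: 1 − 0.90 × 0.90 = 0.19; N = 28; real power 44%.

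At two-sided 0.025 the pattern is the same: for diet-related falls of 5 and 10%, real power is 72 and 56% when the drug effect is 15%, and 60 and 39% when it is 10%.

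**The case against.** **The start of the diet is inferred.** No sentence gives the day on which the instructions are handed out. They could be given at recruitment in WP1, before the urine, and the diet paragraph stands under the main-trial heading. This stands as a limit on certainty: a reader might infer that diet and drug are stated to start together, and the text does not say so. But both diet passages cover all participants, the baseline is placed in a period labelled pre-study, and no on-diet interval before it is described. A leaflet handed out at screening would not by itself provide one.

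**The direction is unknown.** A reader might infer that the drug effect will be inflated. The documents do not support that. The measures in section 2.6.2 do not name an oxalate restriction, section 1.4 directs lower oxalate intake especially to patients at high risk of hyperoxaluric stones, and earlier eating habits are not given. Section 1.4 also says that the same lifestyle changes help prevent cardiovascular disease and diabetes, so some of these participants may already follow similar advice. The diet effect could be small, or in the other direction.

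**The go rule is wider than oxalate.** A reader might infer that a fall in oxalate caused by diet alone would open the main trial. Section 2.6.1 names four analytes, so that does not follow from oxalate alone. The diet can still contribute to the change in each of them.

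**The route to N is not single.** Section 2.3.2 lists a fixed 25% next to the recalculation. If 25% were simply used, the exploratory estimate would not set N. WP3 nevertheless says that N is calculated from the exploratory effect.

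**Dietary deviations are considered in the analysis (section 2.7.4).** That addresses individual departures from the instructions. It cannot remove a change shared by the whole group when there is no control.

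**Conclusion.** The concern holds in a limited form. As described, the exploratory change cannot be divided between dapagliflozin and diet, and that change informs the go decision and the sample-size recalculation. This rests on the natural reading that the instructions do not precede the baseline urine by any set period.

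Size and direction are unknown. With a true drug effect of 15%, assumed diet effects from a 10% fall to a 5% rise move the recalculated N from 20 to 75, against a correct 42. At the lower end real power is 60% instead of 90%. These figures show sensitivity to the assumption and are not a forecast.

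The randomised main-trial comparison is not biased. The point is worth correcting before the first exploratory baseline is taken, because an on-diet baseline cannot be obtained afterwards.

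**What to change.** In section 2.6.1 and WP1, state that the written dietary instructions are given at the start of the four-week pre-study window that section 2.4.1 already uses for pausing interfering drugs. Take the exploratory baseline 24-hour urine at the end of that window, on the diet and before the first dose of study drug. In sections 2.6.1 and 2.3.2 and in WP3, base the go decision and the recalculation on change from this on-diet baseline.

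This needs no new assay and no extra arm, and four weeks fit inside the four-month WP1. The cost is a possible short delay before baseline for participants who have no drug to pause. Where treatment is needed earlier, the investigator's clinical timing takes precedence.

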#### 1.4.4 SGLT-2 inhibitors and urolithiasis.

The current literature provides multiple examples of potential treatment effects of SGLT-2 inhibitors in urolithiasis patients. In clinical trials, it has been shown that SGLT-2 inhibitors – the group of drugs dapagliflozin belongs to – lower serum uric acid [65–67]. A prospective register study by Kristensen et al. with more practically oriented findings included 12,325 patients in both the SGLT-2 inhibitors cohort and the GLP-1 receptor agonists cohort. The incidence of urolithiasis in the SGLT-2 inhibitor cohort was only 49% of the incidence among the GLP-1 receptor agonist cohort. This difference was statistically significant. The incidence of urolithiasis in the SGLT-2 inhibitors cohort was 50% lower compared to the GLP-1 receptor agonists cohort [2.0 per 1,000 person-years vs. 4.0 per 1,000 person-years); the overall incidence difference was 1.9 per 1,000 person-years (95% CI -2.8 – (-1.0)] (HR 0.51; 95% CI 0.37–0.71).

Moreover, 731 patient-pairs with a history of nephrolithiasis and similar baseline characteristics suffered from recurrent urolithiasis; the recurrence-free time was a little longer in the SGLT-2 inhibitor cohort (1,485 vs 1,386 person-years). The incidence of a case of recurrent nephrolithiasis was 36 per 1,000 person-years in the SGLT-2 inhibitor group and 53 per 1,000 person-years in the GLP-1 receptor agonist group. The difference in incidence was -17 per 1,000 person-years [95% CI -33 – (-1.5)] (HR 0.68; 95% CI 0.48–0.97) [68].

Another epidemiological trial targeting the effects of SGLT-2 inhibitors on the nephrolithiasis frequency screening data of 628,570 women 909,628 men and was performed in Japan. They showed a significantly decreased prevalence in men with diabetes mellitus treated with SGLT-2 inhibitors vs. men without one (2.28% vs. 2.54%; odds ratio: 0.89; 95%-CI:0.86–0.94). This difference could be shown over all ages except the men aged 80 years and older [69].

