Furthermore, Anan et al. showed in a rat model the connection between SGLT-2 and nephrolithiasis. They induced calcium oxalate stones by administering ethylene glycol and showed a reduced expression of the SGLT-2 gene and protein as well as an increased level of Osteopontin (OPN] in the cells of the proximal tubules; by adding Phlorizin (predecessor of SGLT-2 inhibitors] the expression of SGLT-2 re-increases and the OPN level decreases. High OPN expression rates lead to calcium oxalate stones-induced damage to the tubules while an additional SGLT-2 inhibitor decreased OPN and reduced the rate of these damages [69].

But OPN in its role as proinflammatory cytokine and effector on the macrophage response [70] in combination with the activation of the transforming growth factor beta (TGFb) pathway is crucial for nephrolithiasis formation and tubular fibrosis [71–75]. In the trial of Anan et al., they found a large turnover of a variety of inflammation participants as well as macrophage infiltration in the cortical interstitial space in the kidneys of the ethylene glycol-treated rats. All the described effects, the high OPN levels, and the intestinal fibrosis following the macrophage infiltration decreased under phlorizin treatment.

Focusing the urine output they showed that the urinary oxalate output between the rats that were stone-induced with ethylene glycol and those that were induced and received an SGLT-2 inhibitor was around one standard deviation (Oxalate in mg/24h urine (mean ± SD): 10.7 ± 0.6 vs. 9.8 ± 1.0). They concluded that SGLT-2 inhibitors have a preventing effect on calcium oxalate stone formations and decrease inflammatory pathways leading to reduced kidney injury and fibrosis [69].

In synopsis, it has been shown that SGLT-2 inhibitors can reduce the urolithiasis frequency over all genders and age groups and they can - lower the oxalate output and the inflammatory pathways in the kidneys with high stone risk. In combination with the shown fact that a reduced calcium oxalate urinary output is associated with a reduced urolithiasis risk and reoccurrence risk, [76] we expect that dapagliflozin can reduce the urinary oxalate/ and or calcium excretion in recurrent urolithiasis patients. We further anticipate that this effect will increase the quality of life and decrease the rate of reoccurrence of the affected patients and the related morbidity and healthcare burden.

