#### 2.2.1 Exploratory phase.

The exploratory phase will focus on metabolomic analyses to identify the effects of dapagliflozin therapy in humans on the urine composition respectively electrolytes and small molecules that may interfere with the urolithiasis frequency such as oxalate, calcium, magnesium, citrate, and uric acid.

Therefore, one group of 22 participants with a diagnosed cardiomyopathy and/or diabetes Mellitus and indication for dapagliflozin will get a daily oral administration of 10mg dapagliflozin combined with regular blood- and urine test to generate data for the calculation of the effect size. Furthermore, we hope to gain more information about the pharmacologic mechanisms of how dapagliflozin modifies the frequency of urolithiasis events in humans as it has been shown in earlier studies [64,68,69].

The SPIRIT-Study workflow and assessment timeline with primary and secondary endpoints have been presented in Fig 1 and S1. Table.

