### 2.3 Sample size calculation

#### 2.3.1 Sample size calculation of the exploratory phase.

As mentioned above, no data exists about the effect of dapagliflozin on the oxalate and calcium 24-hour urine excretion. Given the observed decrease in urolithiasis event rates in previous studies [68,69] and findings from a rat model investigating the impact of SGLT-2 inhibitors on urolithiasis [69] we anticipate a 10%-50% reduction in 24-hour urinary excretion of oxalate and calcium compared to placebo. This expectation is supported by evidence suggesting that a 10% decrease in urinary excretion of calcium and oxalate is linked to a significant 8% reduction in the risk of recurrence [76]. We, therefore, expect a) the effect size of dapagliflozin to be a reduction of urinary excretion of lithogenic molecules between 15% and 25% reduction and b) subsequently to have a clinically relevant potential to lower the risk of urolithiasis reoccurrence.

The sample size calculation is based on our primary outcomes of the intraindividual comparisons. The sample size calculation based on a paired t-test was performed using G*Power Version 3.1.9.4. The significance level of two-sided testing was set to 0.025 to acknowledge the two primary endpoints [80]. We set the power to 90% and the alpha error to 5%. Due to no comparable data, we assume a standard deviation of 20% and a correlation between the intraindividual comparisons of 0.1. Based on the sample size models in Table 1. (assumed effect size of 25%, correlation between the groups of 0.1) we proclaim a group size of 18 participants plus an expected dropout rate of 4 so a total of 22 participants is reasonable.

**Table 1 pone.0322034.t001:** potential group size calculations based on earlier findings.

Mean difference	Mean ± SD group 1	Mean ± SD group 2	Group size	Group size + 20% dropout
10%	1.0 ± 0.2	1.1 ± 0.22	86	104
15%	1.0 ± 0.2	1.15 ± 0.23	42	51
20%	1.0 ± 0.2	1.2 ± 0.24	26	32
25%	1.0 ± 0.2	1.25 ± 0.25	18	22
30%	1.0 ± 0.2	1.3 ± 0.26	14	17

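### The start rule for the main trial requires an undefined positive effect on four urinary analytes, so it can stop the trial although oxalate, its primary endpoint, falls as planned

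*Protocol article*

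**What the plan says.** - **Start rule (2.6.1).** The next part begins solely on condition that the exploratory results show "a positive effect of dapagliflozin on the excretion rate of oxalate, calcium, phosphate, and uric acid". No direction, size or test is attached to a positive effect.
- **Primary endpoint.** Section 2.6 says "The primary endpoint is confirmatory and is the reduction of oxalate in the" active versus the placebo phase. Sections 2.5.1 to 2.5.3 state the hypotheses and primary endpoint for oxalate only.
- **Use of the exploratory data.** Section 2.3.2 and work package 3 recalculate the main-trial size from the oxalate effect.
- **Aim.** Section 1.4.4 says "we expect that dapagliflozin can reduce the urinary oxalate/ and or calcium excretion"; section 2.1 likewise joins the two with and/or.
- **Analytes.** Section 2.2.1 names molecules "such as oxalate, calcium, magnesium, citrate, and uric acid". The secondary endpoints in 2.5.4 list calcium, magnesium, citrate and uric acid. Phosphate is in neither place.
- **Uric acid.** The background evidence in 1.4.4 is that the class can "lower serum uric acid". Nothing is said about which way urinary excretion should move.
- **A conflicting statement.** Section 2.3.1 says "The significance level of two-sided testing was set to 0.025 to acknowledge the two primary endpoints", in a passage about oxalate and calcium.

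**The concern.** The rule decides whether the randomized trial takes place at all. As written it is a conjunction of four analytes, and two of them, phosphate and uric acid, play no part in the primary question. A conjunction passes less often than its oxalate component alone, and the loss is large when an added analyte responds weakly or not at all. Oxalate could fall by the planned amount and the trial still be stopped because phosphate did not move.

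The missing definition adds a second problem. If the wording was meant loosely, the choice between reading it as significance, direction or overall impression would be made after the exploratory data are known.

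**Working it through.** **Inputs from section 2.3.1 and Table 1.** SD 20% of the mean in each group, within-patient correlation 0.1, power 90%, 18 evaluable patients (22 enrolled), planning difference 25%, expected range 15% to 25%. Differences are on Table 1's scale, with the lower mean set to 1.0.

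**Assumptions the document does not supply.** A correlation of 0 to 0.6 between the analytes' changes, and the same SD and within-patient correlation for every analyte.

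**Step 1: reproduce the plan's figure.**
- SD of the paired difference at 25%: √(0.20² + 0.25² − 2 × 0.1 × 0.20 × 0.25) = 0.304.
- Standardised effect: 0.25 / 0.304 = 0.822.
- The paired t-test at two-sided 0.05 and 90% power needs n = 18. All Table 1 rows reproduce at 0.05 (86, 42, 26, 18, 14). At the stated 0.025 they would be 102, 49, 30, 21 and 17. I use 0.05 below because it matches the table.

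**Step 2: oxalate alone, n = 18, two-sided 0.05.** Noncentrality = standardised effect × √18.
- 25%: 0.822 × 4.243 = 3.49, power 0.907.
- 20%: SD 0.297, effect 0.674, noncentrality 2.86, power 0.769.
- 15%: SD 0.289, effect 0.518, noncentrality 2.20, power 0.546.

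**Step 3: all four significant.** With independent changes the pass rate is the fourth power of Step 2: 0.907⁴ ≈ 0.68, 0.769⁴ = 0.35, 0.546⁴ = 0.09. The upper ends come from simulation (40,000 runs) at correlation 0.6.

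| True fall in all four | Four-analyte rule | Oxalate alone |
|---|---|---|
| 25% | 68–77% | 91% |
| 20% | 35–54% | 77% |
| 15% | 9–27% | 55% |

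If oxalate falls 25% and the other three fall 15%, the rule passes 15–32%. With one of the four unaffected it passes about 2%. At two-sided 0.025, four falls of 25% pass 49–64%, against 84% for oxalate alone.

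**Step 4: direction only (each mean moves the right way).**
- All four fall 25%: 99.9%. All four fall 15%: about 95%.
- Oxalate falls 25%, the other three 10%: 81–86%.
- One analyte unaffected, the rest falling 25%: about 1.00 × 0.5 = 50%.
- Two unaffected, the other two falling 25%: 0.5² = 25% if independent; at correlation 0.6, 0.25 + arcsin(0.6)/(2π) = 35%.

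**The case against.** **A stronger reading is tempting: that the rule will usually stop the trial.** The documents do not support it. They define no test and give no expected effect for phosphate or urinary uric acid. If all four fall by 25%, the rule passes more often than not on either reading, and almost always on direction alone. A stop in most cases needs either a significance rule with smaller effects, or a direction rule with at least two analytes unaffected or one moving the wrong way.

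**A reader might also infer that urinary uric acid must rise if serum levels fall, so that the rule almost never passes.** The document gives no such mechanism. What stands is only that the favourable direction for that analyte is not stated.

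**The phosphate point has a limit.** The list in 2.2.1 is introduced as examples, so absence from it is not a contradiction. Absence from the endpoint list in 2.5.4 does stand.

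**Calcium has some claim to be in the rule.** Section 2.3.1 speaks of two primary endpoints in the context of oxalate and calcium. That is an argument for one extra analyte, not three.

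**A sponsor may want a broad favourable urinary profile before starting a crossover.** That is a legitimate choice, but it would have to be stated as the aim, and section 2.1 states a narrower one. A full protocol may define a positive effect more precisely. A definition would settle the size of the problem, but would not remove the mismatch between a four-analyte condition and an oxalate endpoint.

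**Conclusion.** The point holds in this form: the start rule is conjunctive and undefined as written, it does not match the oxalate endpoint, the oxalate-based recalculation or the and/or aim, and it can stop the trial although oxalate falls as planned.

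Under a significance reading, the cost relative to oxalate alone is about 14 to 23 percentage points at a 25% fall in all four (91 − 77 to 91 − 68), 23 to 42 at 20% (77 − 54 to 77 − 35) and 28 to 46 at 15% (55 − 27 to 55 − 9). Under a direction reading the cost is small when all four respond, but about half or more of trials are lost when one or two analytes do not.

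These figures rest on the plan's own SD, correlation and n = 18, on the assumed correlation between analytes, and on carrying the oxalate variability over to the other three.

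**What to change.** Rewrite the start sentence in 2.6.1 so that the decision rests on oxalate. Calcium would be supportive, or co-decisive if the two primary endpoints of 2.3.1 are kept. Report phosphate and uric acid descriptively. Reconcile 2.6.1 with 2.1, 2.3.1 and 2.5.

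The criterion must be fixed in advance and able to fail when there is no effect. Its false-go and go probabilities at n = 18 should be stated. Two examples, with the inputs above:
- **A significant reduction at two-sided 0.05.** False-go 2.5%; go 91%, 77% and 55% at true falls of 25%, 20% and 15%.
- **A point-estimate reduction of at least 10%,** the lower end of the range anticipated in 2.3.1. With no effect the SD of the difference is 0.20 × √(2 × 0.9) = 0.268 and the standard error 0.268/√18 = 0.063, so false-go is P(Z > 1.58) ≈ 6%. Go is 98%, 92% and 77% at true falls of 25%, 20% and 15%.

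Requiring only a reduction whose 95% interval does not exclude 10% would not serve. The half-width is about 2.11 × 0.063 = 13 points, so any observed reduction meets that condition and an ineffective drug passes about half the time.

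The cost is one sentence in 2.6.1 plus the reconciliation. The downside is that the main trial may start with mixed results on the other analytes.
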